### Statistical analysis

SAS (SAS Institute Inc., Cary, NC) and R (version 4.1.2; R Development Core Team, Vienna, Austria) software will be used for all statistical analyses. Continuous variables will be presented as means ± standard deviations or median [interquartile range] and compared by Student’s *t*-test or the Mann–Whitney U-test. Categorical variables will be presented as numbers and percentages and compared by the χ^2^ test or Fisher’s exact test. All tests of significance will be two-sided, with *P* < 0.05 defined as statistically significant.

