**Methods:**

This single center randomized controlled study is designed to evaluate the efficacy of digital healthcare applications for lung cancer patients after thoracoscopic lung resection. A total of 320 patients will be enrolled and randomized 1:1:1:1 into four different groups, with one group each using the smartphone applications NOOM, Walkon, and Efilcare and the fourth being the control group without intervention. Questionnaires will be administered to patients at baseline and after 3, 6, and 12 months. The primary endpoint will be the score on the EuroQol five-dimension index. Secondary endpoints will include other questionnaires about quality of life and dyspnea.

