### Randomization and intervention

The study flow is presented in Fig. 1. The enrolled patients will be stratified according to gender and forced expiratory volume in 1 s (≥ 60% or < 60% of the predicted normal value). The patients will be subsequently randomized 1:1:1:1 to four groups. Allocation to the control or intervention group will be based on the pre computer-generated random number list by a statistician. Following thoracoscopic lobectomy for lung cancer and stabilization, all enrolled patients will participate in education sessions for pulmonary rehabilitation. During these sessions, specialists will teach methods of stretching, aerobic exercise, and muscle training, and recommend an adequate diet [10]. In group A, patients will use the smartphone application NOOM, for 12 weeks. After that, the patients will try to maintain the modified lifestyle. Patients will use Walkon in group B and Efilcare in group C during study periods. Patients in group D will be the control group without any intervention. Enrolled patients will undergo the measurement and questionnaires at index date and after 3, 6, and 12 months. During each visit, attending clinicians will motivate and educate the patients. Allocation concealment will be guaranteed by opaque, sealed envelopes.

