### Data collection and study outcome

At screening, researchers will record patients’ baseline characteristics, including age, sex, smoking history, European Cooperative Oncology Group Performance Status, underlying disease, and previous cancer history. In addition, lung cancer-related information, including pathologic diagnosis, clinical and pathologic stage, and surgery record, will be recorded.

The primary study endpoint will be score on the EuroQol five-dimension (EQ-5D) index, which measures patient quality of life [19]. Secondary endpoints will include body weight and body mass index, as well as measures of pulmonary function and exercise capacity, such as pre- and post-bronchodilator pulmonary function tests, diffusion capacity and 6-min walk tests. Other secondary endpoints will include quality of life questionnaires to evaluate quality of life (Distress Thermometer, Health-Related Quality of Life Instrument with 8 Items, Patient Health Questionnaire-9, Fear of Progression Questionnaire-Short Form, Cancer-related Dysfunctional Beliefs about Sleep, Insomnia Severity Index) and dyspnea degree (modified Medical Research Council dyspnea scale). The timeline of data collection is presented in Table 1.

**Table 1 Tab1:** Timeline of data collection

	Screening and enrollment Index date	Visit 1 3 months	Visit 2 6 months	Visit 3 12 months
Medical history	●			
Chest CT and laboratory tests	●	●	●	●
Informed consent	●			
Body measurements	●	●	●	●
PFT and 6MWT	●	●	●	●
Questionnaires	●	●	●	●

*6MWT* 6-min walk test, *CT* computed tomography, *PFT* pulmonary function test

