### Sample size calculation

We assumed for sample size calculation that effective postoperative rehabilitation could restore the quality of life to a similar level before surgery. A previous lung cancer study showed that the preoperative and postoperative EQ-5D indices were 0.81 ± 0.19 and 0.74 ± 0.11, respectively [20]. Additionally, a minimal clinically important difference in EQ-5D has been observed between 0.03 and 0.05 [21]. Because patients were classified into four groups, the margin of type 1 error was set at 0.008. Calculations showed that a minimum of 76 patients in each group was required to detect a significant difference at the 0.008 level with a power of 0.9 and a dropout rate of 25%.

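### The only comparison named for continuous outcomes, and so by inference for the primary EQ-5D index, is an unadjusted t-test or Mann–Whitney test with no rule between them and no use of baseline EQ-5D or the stratification factors

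*Protocol article*

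**What the plan says.** - **Endpoint** (Data collection and study outcome): "The primary study endpoint will be score on the EuroQol five-dimension (EQ-5D) index".
- **Timing** (Abstract, Methods): "Questionnaires will be administered to patients at baseline and after 3, 6, and 12 months". A baseline value of the primary endpoint is therefore planned for every patient.
- **Stratification** (Randomization and intervention): "The enrolled patients will be stratified according to gender and forced expiratory volume" in 1 s, split at 60% of predicted.
- **Analysis** (Statistical analysis): continuous variables are summarised by mean and SD or by "median [interquartile range] and compared by Student’s *t*-test or the Mann–Whitney U-test". The section names no model, covariate or stratified test, and gives no criterion for choosing between the two tests. It does not mention EQ-5D by name.
- **Planning quantities** (Sample size calculation): "the preoperative and postoperative EQ-5D indices were 0.81 ± 0.19 and 0.74 ± 0.11, respectively", and "a minimal clinically important difference in EQ-5D has been observed between 0.03 and 0.05". The trial is thus sized on a difference in means.

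**The concern.** The design pays for two sources of precision, a baseline measurement of the endpoint and stratified randomisation, and the only analysis named uses neither. If the stratification factors predict EQ-5D, an unadjusted test after stratified randomisation has a standard error that is too large. If baseline EQ-5D predicts follow-up EQ-5D, leaving it out discards variance reduction that costs nothing.

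The second part of the concern is the unranked choice of test. A t-test addresses a difference in means. Mann–Whitney addresses whether values in one group tend to exceed those in the other. With no rule, the target of the primary comparison can be settled after the data are seen. If Mann–Whitney is used, the primary result may carry no mean difference or interval to set against the MCID that the article itself cites.

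**Working it through.** **Inputs from the article.** Means 0.81 and 0.74, so the difference is 0.07. SDs 0.19 and 0.11. Alpha 0.008, two-sided. Power 0.9. Dropout 25%. 320 patients in four equal groups, so 80 per arm and 80 × 0.75 = 60 evaluable.

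**Input not in the article.** The correlation r between baseline and follow-up EQ-5D is assumed, with range 0.3 to 0.7.

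**Step 1: the plan's own figure.** For two independent means, n per group = 2·SD²·(z₁₋α/₂ + z₀.₉)²/δ². With SD 0.11 and δ = 0.07:
- alpha 0.008: 2 × 0.0121 × (2.652 + 1.282)²/0.0049 = 76.4, so 77;
- alpha 0.05/6 = 0.0083: 75.9, so 76.

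The stated 76 therefore matches an unadjusted two-mean formula with the smaller SD and no dropout inflation. With the stated dropout it would be 77/0.75 = 103 per group. This supports reading the plan as an unadjusted comparison.

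**Step 2: unadjusted power at 60 per arm.** The noncentrality is δ/(SD·√(2/60)), with 118 degrees of freedom and a critical t of about 2.70.
- SD 0.11: 0.07/(0.11 × 0.1826) = 3.49, power 0.78.
- SD 0.155, from √((0.19² + 0.11²)/2): 0.07/(0.155 × 0.1826) = 2.47, power 0.41.

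**Step 3: ANCOVA on baseline EQ-5D.** Residual SD = SD·√(1 − r²), with the same power formula. The one degree of freedom spent on the covariate is ignored.

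| r (assumed) | Variance removed (r²) | Equivalent n per arm, 60/(1 − r²) | Power, SD 0.11 | Power, SD 0.155 |
|---|---|---|---|---|
| unadjusted | 0% | 60 | 0.78 | 0.41 |
| 0.3 | 9% | 66 | 0.83 | 0.46 |
| 0.5 | 25% | 80 | 0.905 | 0.56 |
| 0.7 | 49% | 118 | 0.98 | 0.78 |

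At r = 0.5 the adjustment is worth 80 − 60 = 20 evaluable patients per arm.

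**Step 4: a t-test on change from baseline.** The text does not exclude this, and it would use the baseline. With baseline SD s₀ and follow-up SD s₁, the variance of change is s₀² + s₁² − 2r·s₀·s₁. The ANCOVA residual variance is s₁²(1 − r²). The first minus the second is (s₀ − r·s₁)², which is never negative, so change scores are never more efficient than ANCOVA. With equal SDs the factors are 2(1 − r) and 1 − r². At r = 0.5 they are 1.00 and 0.75, so the change score gains nothing over the follow-up score. At r = 0.3 they are 1.40 and 0.91, so it does worse.

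**Step 5: the stratification factors.** The article gives nothing from which to compute the precision gained by adjusting for gender and FEV1. All the gains above come from baseline EQ-5D.

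**The case against.** The strongest reply is that the Statistical analysis section is a generic paragraph in a condensed article. It names neither EQ-5D nor a primary analysis, and covariates are often left to an analysis plan that is not shown. Part of this stands: applying the paragraph to the primary endpoint is an inference. But the article does not stay silent and defer the method. It names one, the only one given for any continuous variable, and the sample size matches an unadjusted formula. That is a stated choice open to comment, though planning unadjusted does not prove that the analysis will be.

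Four stronger readings are tempting, and the article does not support them.

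- **That raw follow-up scores are compared.** The text does not say whether follow-up scores or changes are tested. Step 4 covers both.
- **That a ceiling effect will force Mann–Whitney.** Taking 1.0 as the top of the index (an assumption), it lies (1 − 0.81)/0.19 = 1.0 SD above the preoperative mean, but (1 − 0.74)/0.11 = 2.4 SD above the postoperative one. No normality check is described either. What can be said is only that the choice is left open.
- **That the test causes the low power.** The shortfall comes from the Sample size calculation section: the smaller SD and the missing dropout inflation.
- **That the unadjusted analysis is invalid.** It is valid and, after stratified randomisation, conservative if anything.

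It is also fair to say that the gain from gender and FEV1 may be small. Chronic respiratory disease is an exclusion, so the stratum below 60% of predicted may hold few patients.

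**Conclusion.** The point holds as one of efficiency and clarity, not of validity. The only method named for continuous outcomes leaves baseline EQ-5D and the stratification factors unused, and leaves open whether the primary result will be a mean difference at all.

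The size depends on two unknowns. If the SD is 0.11 and r is about 0.5 or more, baseline adjustment brings power at the planned enrolment back to the intended 0.9. If the SD is 0.155, power stays below 0.8 even at r = 0.7, so adjustment does not replace a correction of the sample size. If r is only 0.3, the gain is about five percentage points at either SD. All these powers assume 60 evaluable patients per arm, a true difference of 0.07 and alpha 0.008. The case for naming a single estimator of the mean difference does not depend on r.

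**What to change.** State in the Statistical analysis section that the primary EQ-5D analysis, at whichever follow-up visit the sponsor designates as primary, is a linear model (ANCOVA) on randomised group, baseline EQ-5D, gender and baseline FEV1, with robust standard errors. It should report adjusted mean differences with confidence intervals, whatever the shape of the distribution, with Mann–Whitney as a sensitivity analysis only. The wording cannot be completed until the primary visit is named, because the article picks none of the 3-, 6- and 12-month assessments.

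The cost is wording alone: EQ-5D, gender and lung function are already recorded at baseline. Recruitment is under way, so the change should be made and dated before any comparison between groups is examined.

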In conclusion, this randomized controlled study is designed to assess the efficacy of smartphone healthcare applications for patients who have undergone thoracoscopic lung resection. In addition, this study will investigate the differences in efficacy among the three applications. Because these applications act via different mechanisms, they may identify the optimal application for patients with lung cancer. This study will likely provide evidence about the efficacy of smartphone healthcare application for digital lifestyle management and improvements in quality of life and exercise capacity via publication. The results of this study may expand the use of digital healthcare application to patients with other types of cancer.

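### The trial is sized at a 0.008 significance level because it has four groups, but the analysis section applies P < 0.05 to all tests and does not exempt the primary EQ-5D comparisons

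*Protocol article*

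**What the plan says.** The Sample size calculation section of the protocol article ties the error level to the number of groups: "Because patients were classified into four groups, the margin of type 1 error was set at 0.008". It then reports that "a minimum of 76 patients in each group was required to detect a significant difference at the 0.008 level". The divisor behind 0.008 is not stated.

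The Statistical analysis section gives one rule: "All tests of significance will be two-sided", with P below "0.05 defined as statistically significant". For continuous variables it names Student's t-test or the Mann–Whitney test, both two-group tests. For categorical variables it names the χ² and Fisher's exact tests, which are not limited to two groups. It does not set the EQ-5D index apart and does not mention adjusted P values.

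On design, Randomization and intervention says: "The patients will be subsequently randomized 1:1:1:1 to four groups". On aims, the Discussion says that, besides assessing efficacy, "this study will investigate the differences in efficacy among the three applications".

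**The concern.** The two sections disagree on when a primary result counts as significant. Under the first, an EQ-5D comparison with P = 0.03 fails; under the second, it succeeds. The universal wording of the second leaves no room to treat the primary endpoint differently.

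The trial's main claims depend on this: whether an application improves quality of life after lobectomy, and whether one application is better than another. The Discussion expects that the trial may identify the best application, which is a conclusion drawn from several comparisons. With both levels in the published text, the threshold could be settled after the P values are known. The more lenient level would also give up the protection for which the sample size was calculated.

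**Working it through.** **1. Where 0.008 comes from.** Four groups form 4 × 3 / 2 = 6 pairs, and 0.05/6 = 0.0083, which is 0.008 to three decimals. Three app-versus-control comparisons would give 0.05/3 = 0.0167, which does not match. The stated level therefore fits an equal split over all six pairs.

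**2. Does the stated sample size use that level?** Inputs from Sample size calculation: "the preoperative and postoperative EQ-5D indices were 0.81 ± 0.19 and 0.74 ± 0.11, respectively", so the difference is 0.81 − 0.74 = 0.07; power is 0.9. The section does not say which SD was used; 0.11 is inferred because it reproduces the stated figure. The formula for two means, two-sided, is

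n per group = 2 × (z₁₋α/₂ + z₀.₉)² × (SD/difference)², with (0.11/0.07)² = 2.469 and z₀.₉ = 1.282.

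| α per comparison | z₁₋α/₂ | n per group, before dropout |
|---|---|---|
| 0.05/6 | 2.638 | 75.9 |
| 0.008 | 2.652 | 76.4 |
| 0.05 | 1.960 | 51.9 |

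The stated 76 is reproduced at the split level as a number before dropout, and not at 0.05. The article presents 76 as allowing for 25% dropout; on these inputs that would need about 76.4/0.75 ≈ 102 to 103. That is a separate question and does not affect this point.

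**3. Family-wise error under each rule.** Assumptions: four equal groups, no true differences, EQ-5D tested at one visit. The pairwise tests share groups and so are correlated. For six pairs, the chance that at least one |t| exceeds the critical value c equals the chance that the studentized range of four means exceeds √2 × c. For large samples at 0.05, √2 × 1.960 = 2.772. Simulation used 400,000 runs at 57 and at 80 patients per group. These sizes are 76 less 25%, and 320/4.

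| Family | Level per test | Chance of at least one false positive |
|---|---|---|
| Six pairs | 0.05 | 20.3% (large-sample range); 20.2% (simulated, both sizes) |
| Three app-versus-control | 0.05 | about 12.5% (simulated) |
| Six pairs | 0.008 | 4.0% (simulated, both sizes) |

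Simpler bounds bracket these. If the tests were independent, 1 − 0.95⁶ = 26.5% for six and 1 − 0.95³ = 14.3% for three. The Bonferroni bounds for six pairs are 6 × 0.05 = 30% and 6 × 0.008 = 4.8%.

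Questionnaires are also given at 3, 6 and 12 months. If each visit were tested separately at 0.05, the error would exceed these figures.

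**The case against.** The best defence is that the two sections can be reconciled. A Bonferroni-adjusted P value compared with 0.05 is the same rule as a raw P value compared with 0.05/6. The 0.05 sentence could thus be a general convention that sits beside the specific level in the sample size section. This is also a condensed journal article, and the details of a multiplicity procedure are commonly left to an analysis plan that is not shown here.

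Part of this stands. A reader might infer that the trial will in fact be analysed without correction and so carries a 20% family-wise error. The article does not establish that. It does not say whether its P values are raw or adjusted, and an unseen plan may apply 0.008. Nor does it declare six primary comparisons. Six is inferred from the value 0.008 and from the app-versus-app aim, and the Discussion states that aim without saying that every pair is a confirmatory EQ-5D test. The 20% is therefore conditional, and 12.5% is the figure for the narrower family.

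What does not stand is the suggestion that this is only an omission. Silence in the analysis section could be put down to condensation. An explicit rule for all tests, at a level different from the one used for sizing, is a contradiction in the published text. The adjusted-P reading is possible, but nothing in the article states it.

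**Conclusion.** The contradiction holds. The article sizes its primary comparison at 0.008 and then sets 0.05 for all tests, so it does not say which level decides a primary result. If the analysis section is read literally, the family-wise error at one visit is about 20% for six pairs, or about 12.5% for the three comparisons with control; six pairs at 0.008 each give about 4.0%. These figures assume equal groups, no true differences and unadjusted P values. They measure the risk under the literal reading and are not an established property of the trial. Because the primary claim depends on which sentence governs, the text should be corrected before the analysis.

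**What to change.** Amend the last sentence of Statistical analysis along these lines:

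*The primary EQ-5D comparisons are the six pairwise comparisons among the four groups, each tested two-sided at 0.008 (0.05/6), the level used for the sample size. Two-sided P < 0.05 applies to the other tests.*

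This names the family, fixes a single level for it and restores the premise of the sample size section. Any separate analysis plan should be checked for the same rule. Enrolment, data collection and the planned number of patients are unaffected. The cost is that primary results with P between 0.008 and 0.05 can no longer be called significant.

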## Discussion

Improvements in exercise capacity and quality of life have been associated with more favorable outcomes in patients with lung cancer [22–24]. Recent advances in digital health care have included smartphone application based pulmonary rehabilitation, which is effective in improving exercise capacity and symptoms in patients with advanced lung cancer [25]. This study is designed to expand the therapeutic potential of smartphone application based pulmonary rehabilitation to patients with early-stage lung cancer who are scheduled to undergo thoracoscopic lung resection and will have reduced lung function and volume after surgery. Although this type of clinical trial is currently uncommon, these trials will likely be more common in the near future, as these interventions can overcome the limitations of medical care within a hospital. This study is designed not only to evaluate the efficacy of smartphone application, but also to compare the efficacy of three different  types of smartphone applications. Patients with early-stage lung cancer usually undergo surgery with curative intent, making management that facilitates prompt recovery more important.

Due to the scarcity of medical resources, most clinicians are interested in acute phase treatment. However, sustainable health care management, such as lifestyle modifications outside the hospital, is also important. Digital intervention can be effective in optimizing patient management. Smartphone applications have several advantages, including their relatively high adherence rates compared with other system. The rates of adherence for weight loss was 93% for smartphone applications, compared with 55% for websites and 53% for diaries [26]. In addition, subjects can monitor their step counts and intensity of walking just by carrying a smartphone [27]. Smartphone applications also allow feedback on a patient's lifestyle, thereby motivating patients [18]. Other advantages of digital interventions using smartphone applications include relatively low medical costs and newly developed expandability [18].

Diet and exercise are also essential for patients after anti-cancer treatment [11]. For these items with smartphone application were well studied in obesity. In these studies, smartphone applications are effective in treating obesity, by reducing and maintaining target body weight [28–30]. The effectiveness of smartphones in obesity resulted from daily life tracking and active feedback on subjects’ diet and exercise patterns. Before discharge, many hospitals instruct patients on diet and exercise after surgery. However, patient compliance with these instructions can be evaluated only during hospital visits, making continuous education and motivation with appropriate feedback difficult. A finding, that the use of smartphone applications can modify the lifestyle of patients with lung cancer, would support the future use of these applications, similar to those in obesity.

The present study will examine three different smartphone applications for lifestyle modification. These applications will likely have effects on patients in different ways. Those randomized to NOOM will be instructed to monitor their diet and exercise patterns every week and encouraged by text messages from human coaches to achieve their target body weights. This protocol assumes that contact via text will produce effects similar to face-to-face contact with supervisors. Users of Walkon will be able to confirm daily step count and the time and intensity of walking. Walkon displays rankings within a group, suggesting that this application will motivate the users through competition. Users of Efilcare will receive pre-written information based on daily records, thus providing individualized information to users. Although each application has been studied in various diseases, few studies to date have compared their efficacy.

In conclusion, this randomized controlled study is designed to assess the efficacy of smartphone healthcare applications for patients who have undergone thoracoscopic lung resection. In addition, this study will investigate the differences in efficacy among the three applications. Because these applications act via different mechanisms, they may identify the optimal application for patients with lung cancer. This study will likely provide evidence about the efficacy of smartphone healthcare application for digital lifestyle management and improvements in quality of life and exercise capacity via publication. The results of this study may expand the use of digital healthcare application to patients with other types of cancer.

